## Abstract

**Background:**

Dementia is a terminal illness and places significant burden on individuals and their caregivers, especially regarding end-of-life decisions for people with dementia (PwD) who lose their decision-making capacity. Current advance healthcare planning concepts fail to consider the psychological processes of decision making. Supported Advance Care Decision-Making (ACD) is a promising approach aiming to enrich existing advance healthcare planning concepts by integrating empowering support strategies and ensuring the success of empowerment. The study aims at providing a feasible and effective approach to enhance ACD in dementia care practice with the goal to increase PwD’s autonomy in making advance care and end-of-life decisions and to reduce proxy burden. It is embedded within Dementia Care Management (DeCM), a routine care measure specifically designed for PwD who live at home.

**Methods:**

The efficacy of supported ACD incorporated in DeCM routine care will be investigated with a single-blind randomized controlled trial. The primary endpoints are the prevalence and validity of advance healthcare planning documents (advance directives or other) and proxy burden at pre vs. post measurement. The secondary endpoints are decisional conflict, patient autonomy, and patient-proxy congruence in preferences.

**Discussion:**

Depending on the results, supported ACD shall be added to the curriculum of DeCM to further increase its effectiveness.

**Trial registration:**

DRKS00036478, 17.04.2025.

**Supplementary Information:**

The online version contains supplementary material available at 10.1186/s12910-025-01290-6.

## Background

Around 1,8 million people suffer from dementia in Germany, with an estimated increase of up to 2 million people within 10 years [1]. The German Hospice and Palliative Care Act (§132g SGB V, 1.12.2015) provides a framework for “Healthcare Planning for the Final Phase of Life”. Such advance healthcare planning^1^ is intended to ensure that individuals receive treatment and care as much as possible in accordance with their wishes, even if they are no longer able to give consent. In general, engaging in advance healthcare planning involves reflection and conversations about one’s own end of life. This is often a taboo topic, which can make it burdensome and anxiety-inducing for individuals and their families [2]. The absence of any form of advance healthcare planning ultimately results in the loss of patient autonomy. It also places a heavy burden on proxy^2^ decision-makers who face uncertainty regarding end-of-life decisions for people with dementia who have lost their decision-making capacity. This underscores the need for advance healthcare planning, with the goal to assist individuals in addressing this taboo topic to autonomously decide on an individually appropriate healthcare plan.

There are various approaches to advance healthcare planning such as advance care planning (often referred to as ACP), one of the most well-known concepts that in recent years has gained increasing relevance. A growing body of evidence demonstrates the effectiveness of advance care planning as a scientifically highly regarded approach to advance healthcare planning. Previous research has shown desirable effects on hospitalization, overall healthcare costs, patient and caregiver satisfaction, as well as on stress, anxiety, and depression in surviving relatives [3, 4]. While research on dementia-specific advance care planning has grown [5], there is still a lack of gerontopsychological research. Much of the effort to improve advance directive completion has focused on creating the perfect document and has overlooked the psychological process of decision-making and people’s wishes regarding the type of planning [6]. Advance care planning discussions align closely with standard practice; however, they often fall short of meeting the informed consent standard and, in many respects, are not suitable for individuals with dementia due to their complexity [7].

This study is part of the DECIDE-2^3^ project and aims to fill this gap by providing and evaluating measures to support the psychological process of decision-making in PwD. We refer to this concept of supported decision-making for advance decisions as *supported advance care decision-making (ACD)*. Conventional strategies for supported decision-making involve elements such as keyword lists and plain language. However, although they enjoy a high level of consensus, particularly among dementia researchers, clear evidence of their effectiveness has yet to be established [8], and experimental studies on supported decision-making, let alone on supported ACD, remain scarce. Within the first funding phase of the DECIDE project, we proposed a home-based, counselling-oriented approach to supported ACD which aims to improve advance healthcare planning for PwD [9]. The DECIDE-2 project builds on this work by offering and evaluating a tailored approach to support the psychological aspects of decision-making processes in advance healthcare planning within routine care.

### Objective

The goal is to increase the autonomy of PwD in making advance care and end-of-life decisions and to reduce proxy burden. We suggest an integrated approach for practical implementation into healthcare (see Study design section).

Our main research questions are: Does supported ACD increase the prevalence and validity of advance healthcare planning documents for PwD living at home more than the gold standard of care?Does supported ACD increase patient autonomy more than the gold standard of care?Does supported ACD decrease proxy burden more than the gold standard of care?We expect that the offer of supported ACD will lead to an increase in the prevalence and validity of advance healthcare planning documents, an increase in patient autonomy, and to a reduction of proxy burden.

This study is the first of two related subprojects of the jointly funded DECIDE-2 project. The overall purpose of this project is to improve advance healthcare planning in dementia care for both individuals with dementia and their proxy decision-makers. In both subprojects, integrated approaches suitable for practical implementation are investigated. In the first study, this involves incorporating Dementia Care Management (DeCM) as a routine-care concept and utilizing it as a vehicle for supported ACD.

The second subproject develops personalized chatbots to support early, easy-to-access ACD for older adults at risk of dementia (age $$65+$$) and proxies of PwD. Using co-design and iterative prototyping, it explores how conversational technology can support end-of-life planning at home. The goal is to help people reflect on their choices, explain them, and share them with loved ones. In a participatory process, the second subproject designs and evaluates conversational technology as a low-barrier, personalized, and ‘private’ way to engaging with ACD, aiming to provide support that facilitates access to additional conversations about the end of life in routine care. The second subproject is not part of this study protocol and will not be addressed further.

## Methods

### Participants

A total of $$N = 150$$ participants will be recruited in the period of March 2025 until January 2027 (see Required sample size and power analysis section for details on calculation and Recruitment section for recruitment details).

Inclusion criteria are a confirmed diagnosis of mild to moderate dementia (F00-F03) or mild cognitive disorder (F06.7), diagnosed by a physician specialised in neurology or psychiatry. The decision on whether to include a person with questionable capacity to consent will be based on a recommended procedure for involving non-consenting individuals in medical research [10]. Participants will be excluded from participation in cases of severe dementia (MMSE score $$< 11$$) and if lack of capacity to consent to study participation persists without an assisting proxy.

Additionally, every participating PwD will choose a trusted individual who will also participate in the study as proxy. If no such person is available, the PwD will still be considered for study participation.

### Intervention

The intervention lies in the *offer* (not mandatory participation) of supported ACD. Supported ACD is the process of supported decision-making and employs an integrated model that combines support (such as elaborated plain language, priority cards, and keyword lists) with capacity assessment. It aims to enable PwD to make self-determined decisions about their own healthcare planning. This involves deciding whether an advance care planning document should be created and, if so, which one. Advance healthcare planning can also mean that a person, after being informed about the various options for advance healthcare planning documents, makes a documented decision not to create such a document. Importantly, our intervention can be understood as an extension of advance healthcare planning (see Integration of supported ACD into advance healthcare planning section) and integrates the value anamnesis, a module of advance healthcare planning, as proposed by Voss [7, 11]. As part of the ACD, a value anamnesis as described in [7] is conducted first (see Fig. 1). This involves documenting general attitudes, values, and experiences related to living and dying, which are recorded in an interview. The next step involves the decision for or against the creation of advance healthcare documents. If a person decides to create advance healthcare documents, the following step is to determine which type of document should be prepared. The individual’s capacity to consent to this decision is documented, and the person with dementia is supported throughout the creation of the advance healthcare document.

**Fig. 1 Fig1:**
[figure not shown]
Integration of supported ACD into the process of advance healthcare planning [7]

### Integration of supported ACD into advance healthcare planning

Supported ACD strives to empower individuals with dementia to make self-determined decisions for or against *any* form of advance healthcare planning^4^. Importantly, the intervention extends the concept of advance healthcare planning, focusing on supported decision-making. As such, supported ACD can be viewed as an empowering module of advance healthcare planning which emphasizes the decision-making process rather than the planning. Aimed specifically to meet the needs of vulnerable individuals, its primary objective is to foster individuals’ capability for decision-making.

Conventional advance healthcare planning concepts lack information about alternative options for health-related advance planning and have recently faced criticism for disregarding the informed consent standard and for their complexity, which hampers their appropriateness for individuals with dementia [7]. Supported ACD aims to enrich advance healthcare planning concepts by integrating empowering support strategies and ensuring the success of this empowerment.

### Study design

This study is designed to compare supported ACD with the current gold standard in routine care for PwD. DeCM is an established routine care approach specifically developed for PwD living at home. We consider DeCM as the gold standard for routine care in Germany, as recently affirmed by its inclusion in the German S3-guideline for dementia. Though not routinely available yet in Germany, it is increasingly being implemented in conventional health care. In DeCM, a dementia care manager – a qualified nurse – visits the PwD at home and develops an individual care plan based on medical, nursing and psychosocial needs of the patient and their family, which are continuously assessed.

A parallel-group design will be used to study the effect of supported ACD within DeCM in a single-blind, randomized pre-post trial. Embedding supported ACD into DeCM allows the blinding of participants, as they will receive gold standard care in both study arms and no prior knowledge of the contents of DeCM is to be expected. No circumstances that require or allow unblinding were determined. Due to ethical reasons, participants in the control group will also receive the offer to receive supported ACD, but only after data collection is completed (to ensure that blinding is preserved). In this case, upon agreement, dementia care managers will again conduct supported ACD, but it will not be part of the study.

By integrating DeCM into both arms of the randomized controlled trial, the independent variable of the design is ACD, allowing us to attribute differences in the outcome to the offer of ACD. In this context, DeCM can be understood more as a vehicle that is well-suited to be complemented by supported ACD. We hereby go beyond a simple effect assessment towards a proof of effectiveness and clinical relevance.

### Randomization

Participants will be randomly assigned to a control (DeCM as routine care) or treatment (DeCM + supported ACD) arm. Randomization will be stratified by gender and study arm. Because previous research indicated increased dropout rates in the supported ACD condition [9], stratified randomization by study arm will be conducted in a 2:1 (treatment:control) ratio, which is expected to result in approximately balanced groups of complete data in the two studyarms. During data collection, the ratio will be monitored and adjusted as needed to ensure balanced groups by the end of the study.

The allocations will be computer-generated using *R* package blockrand [13] with a block size of 9 for studyarm allocation. Separate randomization lists will be kept by gender as well as for each dementia care manager to ensure balanced recruitment ratios across individuals.

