#### Participant retention and withdrawal

To prevent selective drop-out due to cognitive impairments, several strategies will be applied to help participants attend their DeCM appointments. Upon agreement to participate, and if required, participants will receive reminder calls prior to the appointment. Missed appointments will be met with an offer to reschedule. If individuals decide to withdraw from participation, the reasons for dropping out of the study will be collected.

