#### Statistical analyses

Assessment of the prevalence and validity of advance directives will be based on Bayesian generalized linear mixed-effects models. Bayesian estimation is more appropriate than maximum likelihood for smaller sample sizes, when the priors are chosen carefully [44]. We will use probit models modeling the change in the probability of the presence and validity of advance directives over time given the experimental condition and possible covariates (see Outcome measures section).

Outcome variables in these models are a) the binary variable for presence of an advance directive (yes/no), and b) the binary variable for the validity of the advance directive in the sense that it was both voluntarily given and based on informed consent (yes/no). In these models, the condition-by-time interaction and the contrast (whether the pre-post change in the ACD + DeCM condition is more pronounced than in the DeCM condition) are of primary interest. Likewise, analyses of proxy burden and of secondary endpoints will be based on Bayesian linear mixed effects models. Scale scores based on 5-point Likert scale items usually justify the use of ‘normal’ linear mixed effects models. If this is not feasible, the outcomes will be modeled as (ordered) categorical. To avoid loss of sample size, and consequently loss of statistical power, missing data in all model variables will be multiply imputed where appropriate (see Exploratory statistical solution development for missing data and small sample sizes section).

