Despite its strengths, this study also presents several challenges. One key issue is the potential for selective sampling. More severely impaired individuals may be more motivated to participate in the study due to an already heightened awareness of the burdens associated with dementia, possibly leading to a non-representative sample. To ensure voluntary participation, individuals who opt out of the study will continue to receive DeCM as part of routine care. Another challenge is participant retention, given the progressive nature of dementia. Symptom progression may contribute to increased attrition rates and selective drop-out, potentially reducing the sample size and leading to missing-not-at-random (MNAR) data patterns. These challenges will be addressed through an adjusted sampling strategy during recruitment as well as through appropriate statistical methods and insights from related subprojects focusing on missing data. Furthermore, in our study, dementia care managers, rather than physicians or psychotherapists (which is the conventional practice) will assess participants’ capacity to consent. To ensure the validity of the judgments, they will be reviewed by physicians or psychotherapists with expertise in the field in a subsequent sub-study. Finally, the generalizability of the findings may be limited by the study’s regional scope. The results could be influenced by local healthcare policies and care structures, necessitating further research to explore how supported ACD might be adapted to different healthcare settings and geographic contexts.

In summary, this study aims to contribute empirical evidence on the role of supported ACD in dementia care. The findings will help assess whether routine care for PwD can be enhanced through structured decision support and may inform discussions on the broader applicability of ACD in healthcare. Future research should explore the transferability of these findings to different healthcare systems and investigate long-term outcomes associated with the integration of ACD into routine practice.

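### Moving the allocation ratio to equalise completers does not remove attrition bias from the effect of the offer, and it ties study arm to recruitment period

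*Protocol article*

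**What the plan says.** **Allocation.** The Randomization section starts from the observation that "previous research indicated increased dropout rates in the supported ACD condition" and concludes that "stratified randomization by study arm will be conducted in a 2:1 (treatment:control) ratio, which is expected to result in approximately balanced groups of complete data". It then makes the ratio adjustable: "During data collection, the ratio will be monitored and adjusted as needed to ensure balanced groups by the end of the study". It gives no rule for when or by how much the ratio may move. Recruitment runs from March 2025 to January 2027.

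**Target effect.** The Intervention section defines the intervention as the offer of supported ACD, which participants may decline. The Study design section describes the comparison as "allowing us to attribute differences in the outcome to the offer of ACD".

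**Missing data.** Statistical analyses says that "missing data in all model variables will be multiply imputed where appropriate". It refers to a methodological side project that cites evidence for multiple imputation under MAR but will also study fully Bayesian and maximum likelihood approaches. The models contain condition, time and possible covariates; no term for recruitment or ratio period is named.

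**Selective loss.** The Discussion foresees attrition "potentially reducing the sample size and leading to missing-not-at-random (MNAR) data patterns" and answers: "These challenges will be addressed through an adjusted sampling strategy during recruitment as well as through appropriate statistical methods".

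**Retention.** The section on participant retention provides reminder calls and collection of dropout reasons, and "Missed appointments will be met with an offer to reschedule". It does not say whether T2 is sought from someone who stops ACD.

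**The concern.** A person who is offered ACD and leaves is part of the effect of the offer. Randomising more people into the arm with the higher loss replaces the missing numbers but not the missing people. If those who leave differ from those who stay, equal completer groups are as biased as unequal ones. Adjusted sampling therefore cannot do what the Discussion asks of it.

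Moving the ratio adds a second, avoidable problem. If the share allocated to ACD differs between early and late recruitment, anything that changes the six-month course of participants over that time becomes associated with arm. Within a period of constant ratio the comparison is sound; pooled over periods without adjustment it is not.

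The relevance threshold is a rise of about 20 to 30 percentage points. At stake is whether a result that reaches it describes the offer or only the people who completed ACD.

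**Working it through.** **Inputs from the protocol:** N = 150; 2:1 allocation; baseline document prevalence about 50%; relevant gain 20 to 30 points; T2 six months after T1.

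**Assumed, because not stated:** dropout rates, the outcome of leavers, the time and size of any ratio change, and drift over recruitment.

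**The plan's own sample size.** About 150 cannot be reproduced exactly, because alpha, the variance components and the size of a moderate effect are not given. The nearest simple variant (standardised difference 0.5, 2:1, two-sided 5%) gives 144. This does not affect the point.

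**1. What 2:1 implies about loss.** Of 150, 100 go to ACD and 50 to control. Equal completers require 100 × r(ACD) = 50 × r(control), so r(ACD) = r(control)/2, where r is retention.

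| Control loss | Implied ACD loss | Completers per arm |
|---|---|---|
| 0% | 50% | 50 |
| 10% | 55% | 45 |
| 20% | 60% | 40 |

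This is inferred from the purpose given for the ratio; it is not a stated dropout rate.

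**2. Bias from a moving ratio.** Bias = (late-recruited share in ACD − late-recruited share in control) × drift in the pre-post change between periods. Take a switch after 75 participants, with 50 ACD and 25 control before it.

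- Switch to 1:1: the late period adds 37.5 and 37.5. Late shares are 37.5/87.5 = 0.429 and 37.5/62.5 = 0.600, a difference of −0.171. A 10-point drift gives −1.7 points.
- Switch to 1:2: the late period adds 25 and 50. Late shares are 25/75 = 0.333 and 50/75 = 0.667, a difference of −0.333. A 10-point drift gives −3.3 points.
- Switch to 3:1: the late period adds 56.25 and 18.75. Late shares are 56.25/106.25 = 0.529 and 18.75/43.75 = 0.429, a difference of +0.101. A 10-point drift gives +1.0 point.

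A drift of opposite sign reverses each result. With a constant ratio, or with analysis stratified by ratio period, the bias is 0.

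**3. A separate mechanism: imputing ACD leavers from ACD completers.** Let r be ACD retention and f the share of the completers' benefit that leavers still obtain. The offer effect is the completer effect × [r + (1 − r)f], so the inflation factor is 1/[r + (1 − r)f].

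| ACD retention | f = 0 | f = 0.5 | f = 1 |
|---|---|---|---|
| 70% | 1.43 | 1.18 | 1.0 |
| 50% | 2.0 | 1.33 | 1.0 |
| 40% | 2.5 | 1/0.7 = 1.43 | 1.0 |

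A simulation (600 runs, 20 imputations, 100:50, imputation by arm and baseline status, leavers changing like controls) gave, in percentage points:

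| Loss ACD/control | Gain, ACD completers | Gain, control | Within-arm MAR | Full follow-up | Control-based imputation |
|---|---|---|---|---|---|
| 50%/0% | 20 | 0 | 19.7 | 10.1 | 10.1 |
| 50%/0% | 30 | 0 | 29.7 | 15.2 | 15.2 |
| 30%/10% | 20 | 5 | 14.9 | 10.6 | 10.6 |

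In the first two rows the MAR estimate lies at the limits of the relevance range while the effect of the offer is about half of it.

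**The case against.** The strongest reply is that little of this is settled. No dropout rate is stated, and balance is only expected to be approximate, so 50% ACD loss is an inference. MAR appears as a summary of earlier research; the side project is meant to guide the final choice, the Discussion acknowledges MNAR, and imputation models are commonly left to a statistical analysis plan. All of that stands. It rules out saying that the trial will double its effect.

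Leavers may also have benefited. ACD1 falls within 30 days of T1 and ACD2 within a further 15, so ACD can be finished about 45 days after T1, with T2 at six months. Someone lost after ACD2 may already hold a document. This also stands: f = 0 is the extreme case. Carrying T1 status forward in the ACD arm as the main analysis would count such documents as absent.

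The calendar effect is conditional and small. It needs an actual ratio change, drift in the pre-post change (drift in baseline prevalence largely cancels in the condition-by-time interaction) and an analysis without period, which the reference to possible covariates does not exclude. This limits the size but does not justify an open-ended ratio.

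Finally, T2 is already planned for both arms, and nothing says that declining ACD ends participation. Only an explicit statement is missing.

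A reader might also infer that changing the ratio contradicts randomisation lists fixed in advance. The text says only that allocations are computer-generated in blocks of 9; new lists could be produced for a new ratio.

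**Conclusion.** The point holds for what the protocol does state: an adjustable ratio aimed at completer balance, and adjusted sampling named as a remedy for selective drop-out. Neither removes attrition bias from the effect of the offer. The adjustable ratio adds a bias of 1.7 points (to 1:1) or 3.3 points (to 1:2) per 10-point drift, in either direction, assuming a halfway switch, drift common to both arms and no adjustment for period.

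A reader might infer that shifting the ratio can double the estimated effect. It cannot. A factor of 2 comes only from completer-type or within-arm MAR estimation, with 50% ACD loss and no benefit in leavers. Over the settings examined the factor runs from 1.0 to about 2.5, and the protocol does not commit to that imputation. The matter should be corrected because the correction is cheap, but it does not invalidate the trial.

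**What to change.** 1. Hold 2:1 for all participants. If the ratio has been or will be changed, enter ratio period as a stratum in every model, including its interaction with time, because the drift that matters is in the pre-post change. Remove completer balance as a remedy for selective drop-out.
2. State that T2 is sought in every randomised participant, whether or not ACD was accepted or finished. T2 is a DeCM visit in both arms.
3. Beside the MAR result, report control-based (reference-based) multiple imputation as a sensitivity analysis for both primary endpoints, document status and proxy burden. Use document status at ACD2 where known. Only the fact that a document was created is needed, since the Material section leaves the documents themselves with participants. Do not use one-arm carry-forward as the main analysis.

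**Cost:** protocol wording, T2 visits that are already scheduled, and one further imputation run. Completer numbers may be unequal, with some loss of precision. The control-based estimate may be conservative if leavers did benefit.
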